**Nonclinical programs**			
	Messaging campaigns	Digital or physical messaging, social marketing aimed at raising awareness about PrEP or sharing information about PrEP services available	
	PrEP outreach and education	Nonclinical outreach and education activities, typically delivered by staff or peers at community-based organizations focusing on raising awareness about PrEP, addressing misinformation, and sharing information about the availability of PrEP	

^a^Health jurisdictions program settings (in-clinic, external clinic, and nonclinical) with corresponding program types and program details. The program types will be assessed to understand which programs were implemented in each jurisdiction over time and the level of resources committed to each to obtain program data.

^b^PrEP: pre-exposure prophylaxis.

^c^EHR: electronic health record.

^d^STI: sexually transmitted infection.

We will also gather information on the passage and implementation of policies regarding PrEP at the state level through a systematic review of legislative records in existing state public health statutes and the legal database Westlaw. Data will be extracted, if available, regarding program types, program start or end dates, funding agencies, jurisdictions implementing the program, the program implementers, and the program financial expenditures. To improve data quality, we will optimize interrater reliability through clear definitions of domains, use raters who are familiar with the content area, and provide thorough training for raters through practice-based learning sessions. Validation of the dataset will be accomplished through conducting parallel extraction of independent coders to determine intercoder agreement for a proportion of the dataset.

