To understand the impact of PrEP policies and programs (objective 2), we will leverage the legal coding and health jurisdiction program provision datasets described above to conduct quasi-experiments with outcomes of PrEP starts, PnR, and retention in care. PrEP programs have been adopted by local health authorities in the context of the disbursement of EHE funds as grants to applicants. Despite the lack of random assignment of jurisdictions to policies and programs, we propose a quasi-experimental design that allows us to have findings that reflect several of the characteristics of randomized studies, including temporality and controlling for time-invariant factors. Although quasi-experimental approaches are subject to some limitations inherent to nonrandomized designs such as challenges in controlling for time-varying characteristics, these designs minimize bias relative to other analysis approaches. Moreover, quasi-experimental approaches improve upon the external validity of randomized studies because the data stem from programs that have been enacted in practice. Because of the study design, results will be well positioned to inform real-world programs such as those that comprise EHE efforts. For quasi-experiments, we will conduct analyses using methods such as difference-in-differences (DID) that account for intervention and control jurisdiction trends before program implementation. Because interventions are implemented at different points in time, we will use the heterogeneous DID method proposed by Callaway and Sant’Anna [32] or a similar method to account for potential confounding from multiple implementation periods. Health jurisdictions implementing a program or policy will be the primary intervention unit, and controls will be jurisdictions not implementing a program. DID analyses will be accomplished with regressions that include a term for group (eg, telemedicine PrEP program or not), period (month), and group-by-period interactions that serve to estimate the effect of the intervention. Our approach provides a relatively large sample size for such analyses, with many of the 50 counties or local jurisdictions funded under the EHE program implementing programs under assessment, and other non-EHE jurisdictions also implementing some of the identified programs. Control jurisdictions will be counties or states in the United States that do not implement a particular program, using 9 years of monthly PrEP use data (2016-2024). Depending on characteristics of the intervention, such as statewide provision, we may restrict the control group to jurisdictions meeting certain criteria in order to improve the match between intervention and control groups. For instance, we might match counties by HIV prevalence or jurisdiction size.

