
Although we have conducted substantial outreach to health jurisdictions to optimize engagement, we anticipate that there will be some missing data from the health jurisdiction survey. It is likely not a valid approach to impute data on whether a program was implemented in a particular jurisdiction. Therefore, analyses will be conducted only among jurisdictions providing data. To explore the impact of the missingness, we will assess descriptive differences between missing and nonmissing jurisdictions for the outcome over time and for key sociodemographic variables. Our outcome assessment will include the determination of policy impacts on PnR, an equity metric. Additionally, we will identify potential inequities in PrEP use based on key geographic, socioeconomic, and demographic characteristics. This may be conducted empirically with interaction terms between the policies of interest and these characteristics. DID models assume that trends in the intervention and control groups are parallel before the intervention. This is a critical consideration because control jurisdictions might have additional interventions to the one under consideration. We will seek to assess the validity of this premise, using techniques such as visual assessments of event-study plots and the Granger causality test to determine whether the design is sufficient to meet the parallel trends assumption. If parallel trends assumptions are not met, we will consider alternative approaches such as multivariable matching, lagged dependent variable regression, and synthetic control models (adapted for multiple treated units). The synthetic control method uses a matching algorithm to create a weighted dataset for the control (nonintervention) group, assigning a weight to each element in the group to eliminate prior differences in critical covariates and the outcome. Another option is to use difference-in-difference-in-differences (DDD) to assess the additional change from a specific policy (eg, telemedicine) above and beyond the overall EHE program effect for funded EHE jurisdictions. The nature of the DID and DDD designs controls for confounders that do not vary over time. Therefore, to optimize model efficiency, we will not control for variables expected to remain constant over time (eg, area-level poverty), only adding time-variant covariates. To further ascertain the validity of the DID approach, we will conduct placebo tests for policies that our models have found to have statistically significant effects on PrEP use. These tests assign earlier implementation dates selected at random (eg, false) to treated units to observe if we continue to reject the null hypothesis under these “false” implementation dates. Statistically insignificant results from the placebo tests will increase confidence that the model outcomes are valid. Further, we will assess the sensitivity of our models to the implementation time period by conducting the Bacon-Goodman [33] decomposition and reporting any disproportionate influence of certain implementation periods. We will seek to conduct additional sensitivity analyses that explore whether funding levels determine the impact of programs, with the program intervention variable being related to prevention budget expended rather than whether the program was enacted. Analyses will be conducted in SAS 9.4, STATA 19, or similar software. Given that there are multiple policies, it will be critical to address challenges with multiple comparisons. To accomplish this, we will, where possible, seek unified model approaches that simultaneously test the effects of multiple programs.

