### Anticipated Research Timeline

Extraction of PrEP prescription and procedure claims was completed as part of objective 1 in 2025. Following this critical component, the planned analyses listed under objectives 1-3 in Table 3 will be conducted. This timeline provides detailed information about the planned analyses for the grant, although we may add additional analyses as new products (eg, long-acting lenacapavir) come to market or new programs, policies, or their cessation occur over time.

**Table 3 table3:** PrEP (pre-exposure prophylaxis) Epidemiology, Modeling, and Surveillance (PREMISE) anticipated timeline and research activities across the 5-year grant period^a^.

Activities			Year																					Data source			Planned analyses
			1				2				3				4				5								
			<>		<>		<>		<>		<>		<>		<>		<>		<>		<>						

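### The written DID regression is not reconciled with the staggered-start method named just before it, and the placebo-date test does not exclude months after the true start

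*Protocol article*

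**What the plan says.** All of this is in the protocol article, mostly in Data Analyses (Objective 2).

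- **Named method.** "Because interventions are implemented at different points in time, we will use the heterogeneous DID method" of Callaway and Sant'Anna, "or a similar method to account for potential confounding from multiple implementation periods".
- **Written regression, two sentences later.** "DID analyses will be accomplished with regressions that include a term for group (eg, telemedicine PrEP program or not), period (month), and group-by-period interactions", with the interactions serving as the effect estimate. Controls are jurisdictions that do not run the program, so group is a fixed yes/no attribute.
- **Timing check.** A Goodman-Bacon decomposition is planned, "reporting any disproportionate influence of certain implementation periods".
- **Placebo test.** For policies found significant, "These tests assign earlier implementation dates selected at random (eg, false) to treated units". A non-significant result is taken as support for the model.
- **Program endings.** The policy extraction described under Health Jurisdiction Survey covers "program start or end dates" where available. Anticipated Research Timeline says analyses may be added as "new programs, policies, or their cessation occur over time".

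**The concern.** The two descriptions are different models. A cohort-based estimator compares each jurisdiction with controls from its own start date. A program-or-not indicator crossed with month pools, in each month's coefficient, implementing jurisdictions already running the program with those that have not begun. The power calculation also rests on a time-by-treatment interaction, which resembles the simpler model, so the rest of the article does not settle the matter.

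The placebo test has a separate problem. If the outcome series still contains the months after the true start, a false earlier date creates a post-period that includes the real effect. The test may then reject because the program works, not because trends were unequal.

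The Objective 2 estimates feed the Objective 3 transmission and cost-effectiveness models. A diluted effect would understate infections averted. Because dilution depends on how widely a program's starts are spread, it could also change how programs rank. A contaminated placebo test would lower confidence in effective programs.

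**Working it through.** The article attaches no figure to the DID specification, so there is none to reproduce. The illustrations borrow three figures from Power Calculation: Objective 2 (6 implementing counties, 238 controls, a difference of 2.4 starts per 100,000) and the 108 months of 2016-2024. Start dates are assumed.

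**1. Dilution under the literal regression**

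Assume parallel trends and a constant effect τ. The group-by-month interaction in month t, relative to months before the first start, is τ × (share of implementing counties already started in month t). Averaged from the first start to month 108, it is τ × (started county-months ÷ all implementing county-months).

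Put the first start in month 49 (January 2020) and space the six starts evenly. The denominator is 6 × 60 = 360.

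| Assumed starts | Started county-months | Share | τ = 2.4 becomes |
|---|---|---|---|
| All in month 49 | 360 | 100% | 2.40 |
| Over 2020-2021 | 60+55+51+46+42+37 = 291 | 81% | 1.94 |
| Over 2020-2022 | 60+53+46+39+32+25 = 255 | 71% | 1.70 |
| Over 2020-2024 | 60+48+36+25+13+1 = 183 | 51% | 1.22 |

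Dilution is therefore 0%, 19%, 29% and 49%.

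Single-month coefficients follow the same rule: 2.4 × 1/6 = 0.40 when one county has started, 2.4 × 3/6 = 1.20 at three, and 2.40 once all have. Only the last is undiluted.

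A noiseless panel of 6 and 238 counties, with last starts 0, 12, 24, 36 and 48 months after the first, gave literal averages of 2.40, 2.16, 1.92, 1.68 and 1.44. Cohort-by-month estimation against never-implementing counties returned 2.40 every time. With an effect that grows over 24 months and a 48-month spread, the true average was 1.66, the cohort-by-month estimate 1.66 and the literal average 1.00.

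**2. Placebo dates**

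Take a county that truly starts in month s and give it a false start p < s. With all months kept, the placebo post-minus-pre contrast has expectation τ × (109 − s) ÷ (109 − p). For s = 67 and p = 37 this is 2.4 × 42/72 = 1.40, although nothing happened at month 37. If the series stops at month s − 1, the expectation is 0.

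Simulation with 6 and 238 counties, effect 2.4, and assumed starts over three years, county-month SD 6 and autocorrelation 0.3:

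- SD 6 gives the main test about 90% power for 2.4, in line with the article's stated power.
- Post-start months kept: the placebo rejects in about 49% of runs, and in 52% of runs whose main result was significant (the only ones in which the article would apply it).
- Truncated at the true start: about 5%.
- Varying the spread of starts at SD 6: 33% to 57% untruncated, 5% to 7% truncated.
- Varying the noise in a similar simulation, untruncated: 52% at SD 6, 18% at SD 12, 10% at SD 20, 6% at SD 73.

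**The case against.** **On the regression.** The explicit commitment for staggered starts is to heterogeneous DID or similar. The later sentence can be read as a generic account of DID, and cohort-by-period regressions are one way to fit such estimators. The article collects dates of program operation and plans event-study plots, so it is aware of timing. It gives no start dates and does not say the interactions are averaged. All of this stands. A reader might infer that the article contradicts itself outright, or that a diluted analysis will be run. The text supports neither, only that two descriptions sit unreconciled.

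**On the placebo test.** The article does not say that post-start months are kept, and SD 6 and autocorrelation 0.3 are not in it. The one county SD it states is 73, for PrEP use and not necessarily for monthly starts; at that value the untruncated rejection rate is 6%. So a single rate should not be quoted without its range. SD 6 is nonetheless a reasoned choice, because it reproduces the stated power. At larger SDs the same main test would fall short of that power. Silence is also not harmless here: the rule for reading the test is stated, and it is sound only if the series is truncated.

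**On the other checks.** A reader might infer that the Goodman-Bacon decomposition is an error, or that months after a program ends will be counted as treated. Neither follows. The decomposition can be run on a companion two-way fixed-effects model, and the article states no rule for months after a program ends. Its allowance for a similar method leaves room for estimators that permit exit.

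**Conclusion.** The point holds as two specific defects of wording.

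1. The regression sentence, taken literally, is not the staggered-start estimator named before it, and nothing says which governs. The dilution is conditional on that literal reading and on averaging from the first start. It is 0% with simultaneous starts and about 20% to 50% under the assumed 2- to 5-year spreads. The true spread is not in the article, so no figure can be assigned to any actual program.
2. The placebo test is not limited to months before the true start. At noise consistent with the stated power, it would reject in about half of runs for a program with a real effect of 2.4, against about 5% when truncated. The rate approaches the nominal level as noise rises. This defect does not depend on which DID model is used.

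The decomposition and the handling of program endings are minor clarifications and do not carry the point.

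**What to change.** - **Regression sentence.** Replace it with a statement that effects are estimated by adoption cohort and month, with not-yet-implementing and never-implementing jurisdictions as controls, and then averaged over time since start.
- **Placebo test.** State that false dates are drawn, and the test run, only on months before each jurisdiction's true start.
- **Minor.** Label any Goodman-Bacon decomposition as describing a companion two-way fixed-effects model. If programs end, say whether a jurisdiction is censored at its end date or an estimator that allows exit is used.

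The cost is a few sentences and standard options in existing software. Start dates are already being collected. Censoring at program end would lose a small number of late months.

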
#### Power Calculation: Objective 2

The study design achieves 90% power to detect a minimum difference between intervention and control county PrEP rate means of 2.4 PrEP starts per 100,000 population. This is based on a sample size of 8,784,000 county-person-month observations, a figure obtained from a minimum estimate of 6 counties implementing a particular program and 238 control counties not implementing the program. We assume that each county has an average of 300 individual PrEP users (a conservative estimate because the 2021 average and median county PrEP users are 1210 and 482), and we assume an average of 60 months of follow-up (a conservative estimate because the total follow-up period is 144 months). The standard deviation of PrEP use at the county level is 73, and we conservatively assumed a small (0.05) within-person correlation. The power assessment is based on a time-by-treatment interaction test using a mixed-model analysis with a significance of 0.05. We performed a similar analysis for state-level policies and found a minimum detectable difference of <3 additional PrEP starts. Power calculations were performed in PASS 2022.

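### For programs near the stated minimum of 6 implementing counties, the named DID method's usual large-sample inference would give intervals that are too narrow and a two-sided false-positive rate of about 13% instead of 5%

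*Protocol article*

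**What the plan says.** Under Data Analyses, the protocol article makes health jurisdictions the unit of intervention for objective 2. For staggered start dates it states "we will use the heterogeneous DID method proposed by" Callaway and Sant'Anna, and it also allows a similar method. It adds: "Our approach provides a relatively large sample size for such analyses". The reason given is that many of about 50 EHE-funded jurisdictions, and some others, run the programs in question.

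Power Calculation: Objective 2 sets a floor of "a minimum estimate of 6 counties implementing a particular program and 238 control counties not implementing the program". The stated test is a "time-by-treatment interaction test using a mixed-model analysis with a significance of 0.05". The sample is counted as "a sample size of 8,784,000 county-person-month observations", and the only correlation allowed for is 0.05 within person.

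The article gives no standard error, bootstrap or reference distribution for the effect test. The validity checks under Data Analyses are event-study plots, a Granger test, placebo dates and the Bacon-Goodman decomposition. Analyses are limited to jurisdictions that answer the survey, which can only lower the number of treated units.

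**The concern.** A DID contrast of 6 treated with 238 control counties is limited by the 6. The named method's usual inference treats the treated-side variance as known, which is reasonable with many treated units and not with 6. The power section counts millions of person-months, which suggests that the county-level limit was not in view.

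What is at stake is the reliability of the significance call and of the interval for a program with few implementers. Significance explicitly decides which policies receive placebo tests. The programs judged effective in objective 2 then go into the objective 3 models.

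**Working it through.** **The plan's own figures.** (6 + 238) counties × 300 users × 60 months = 4,392,000. This is half of the stated 8,784,000, which would need 120 months or some other factor of 2. The detectable difference of 2.4 was not reproduced: simple mean-difference formulas gave 0.5 to 1.5, and pre-post DID with a design effect gave 2.7 to 2.9. The PASS settings are not given, so 2.4 is not called wrong. The point below does not depend on it.

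**Inputs.** From the article: 6 treated and 238 control counties, significance 0.05, and 60 months (power section) or 108 months (2016-2024). Assumed: a two-sided test, the named method's usual influence-function SE or multiplier bootstrap, the 1.96 critical value, and roughly normal county changes with equal variances.

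**Step 1: where the uncertainty comes from.** With equal variances, the treated share of the variance is (1/6) / (1/6 + 1/238) = 238/244 = 97.5%.

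**Step 2: closed form, one start date.** The influence-function variance divides by n, not n-1. Ignoring the small control-side term, the statistic behaves as t on n-1 df multiplied by √(n/(n-1)). It rejects when |t on n-1 df| > 1.96 × √((n-1)/n).
- n = 6: threshold 1.96 × √(5/6) = 1.789; P(|t on 5 df| > 1.789) = 13.4%.
- n = 10: threshold 1.96 × √0.90 = 1.859; 9.6%.
- n = 20: threshold 1.96 × √0.95 = 1.910; 7.1%.
- n = 6 with an n-1 divisor but still 1.96: P(|t on 5 df| > 1.96) = 10.7%, so the divisor alone does not cure it.

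**Step 3: simulation with no program effect.**

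| Setting | Two-sided rejection at nominal 5% |
|---|---|
| 6 v 238 county-level changes | 12.9% (6.4% favorable, against 2.5% nominal) |
| Full group-time estimator, one start date, analytic SE | 11.6-14.1% |
| Same, multiplier bootstrap | 13.7-15.6% |
| Full estimator, two or three start dates | 13.3-16.6% |
| 10 treated | 9.2% |
| 20 treated | 6.7% |
| 30 treated | 6.1% |
| 50 treated | 5.6% |

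The full-estimator runs used 60 or 108 months and serial correlation of 0.05, 0.5 or 0.9. Neither factor changed the picture. Coverage at 6 counties is 100% - 13% = about 87%.

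**Step 4: other distributions, 6 treated.** Heavier tails gave 11.9%. Strong right skew (lognormal) gave 23.6%, but only 0.8% in the favorable direction.

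**Step 5: candidate remedies, 6 treated.** The n/(n-1) correction with a t reference on 5 df gave 4.2% to 5.0%. With unequal treated and control variances it gave 4.7% to 4.8%. A pooled-variance test, which approximates permuting program status, gave 5.0% with equal variances. It gave 0.6% when the treated SD is 0.7 times the control SD, about 15% at 1.4 times and 31% at 2 times.

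**Step 6: do the planned checks help?** Placebo dates are applied only to findings already significant, and they reuse the same few treated counties. Event-study plots and the Granger test address parallel trends. The decomposition addresses the influence of particular implementation periods. None changes the reference distribution of the main test.

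**The case against.** The strongest reply is that the faulted test is inferred. The article names no variance estimator, allows a similar method, also describes regressions with group-by-period terms, and takes its 0.05 from a mixed-model power test. An article may leave small-sample inference to a fuller plan. Under equal variances a pooled county-level regression rejects 5.0%, so the excess arises only when the treated-side variance is estimated from 6 counties and referred to a normal. All of this stands, and it makes the finding conditional. It does not remove it. The named method, run in its usual way at the article's own floor, is oversized, and the pooled alternative is safe only when treated and control variances agree.

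Four stronger readings are tempting, and the document does not support them.
- **The sample-size statement is simply wrong.** Its stated basis is wide adoption among about 50 EHE jurisdictions, where the excess is small. Six is a worst case, and no program is said to have only 6 implementers.
- **Ineffective programs will be declared effective 13% of the time.** About half of the false rejections are favorable, and fewer under right skew.
- **Too-narrow intervals are passed to the cost-effectiveness model.** The article says that effect and cost estimates inform the model. It does not mention intervals.
- **Significance alone defines an effective program for objective 3.** The article does not say so, and its Limitations section adds effect size, dose-response and plausibility to the causal judgement.

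**Conclusion.** The point holds in conditional form. If the named method's usual normal-reference inference is used, a program with 6 implementing counties has a two-sided true-null rejection of about 13% (somewhat more with staggered starts) and 95% interval coverage of about 87%. Rejection in the favorable direction is about 6% against 2.5%, provided county changes are roughly symmetric. The two-sided rate is about 9% at 10 treated counties and about 7% at 20, and approaches nominal for widely adopted programs. The sizes assume roughly normal changes with equal variances. Direction depends on symmetry, but the two-sided rate exceeded 5% in every distribution tried. This concerns the effect test and its interval for programs with few implementers. It says nothing about the power figure and does not impugn every objective 2 analysis. It should be settled before those programs are analyzed.

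**What to change.** Under Data Analyses, add a rule for programs with few implementing jurisdictions, for example fewer than about 20. Base p-values and intervals on county-level SEs with the n/(n-1) correction, and refer them to a t distribution with df equal to implementing jurisdictions minus 1. The cutoff is a judgement: symmetric changes give about 7% at 20, and strong skew gives more.

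Use randomization inference only as a supplement, among matched or similar-sized jurisdictions and with a studentized statistic, because unequal variances can throw it further off than the problem it is meant to solve.

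Report the number of implementing jurisdictions beside each estimate. Keep the sample-size sentence, and add that it does not hold for programs near the stated minimum.

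The cost is a few sentences and a small change to the inference step. Intervals widen for the affected programs: at 6 counties the critical value is 2.57 instead of 1.96 and, with the variance correction, 2.57 × √(6/5) / 1.96 = 1.44, so about 44% wider. Power for those programs falls accordingly.
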